**Fig. 1 Fig1:**
[figure not shown]
Phase 2 randomized controlled trial study flow

**Fig. 2 Fig2:**
[figure not shown]
SPIRIT flow diagram of the RCT schedule of enrollment, interventions, and assessments

### Phase 1 documentation of drinking norms and student testimonials

In the first phase of this project, we collected normative drinking data from 2650 study abroad students from 65 universities and colleges. Normative drinking by gender and by country will be presented in the intervention. Based on our prior work, we expected norms to be generally moderate and they will be displayed in a manner that documents that the majority of students abroad drink moderately rather than heavily. The PNF serves to correct misperceived norms and participants see that their intended drinking at predeparture, as well as their perceptions of peer drinking, may be more than the actual drinking of their peers abroad. In addition, we proposed to interview study abroad students about their experiences with drinking (both by peers and by local people) and experiences with sojourner adjustment abroad. Selected clips from these interviews will be loaded into the intervention template so RCT student participants can hear about moderate drinking abroad, such as how local people view alcohol as a complement to a meal rather than as a means to get intoxicated, and how peers that spent most of their time in bars with other Americans risk missing out on meaningful social and cultural experiences.

Video clips will also display students discussing ways in which they engaged with the culture while abroad, with content focused on facets of sojourner adjustment [77]. For example, clips will show students discussing tips and strategies for how they started conversations with local people, how they found out about local cultural events, what they did to help themselves feel more like a local person rather than a tourist, and how they overcame anxiety about using the local language and strengthened their cultural experience by practicing with local people. Negative sojourner adjustment will also be addressed, with clips of students discussing how they expanded beyond their American student network while abroad and how they managed feelings of homesickness and “culture shock” while abroad. Lastly, video clips will feature students describing ways in which they stayed safe while abroad, with an emphasis on prevention of sexual violence victimization abroad. Students will discuss avoiding unwanted sexual experiences, tips for protecting oneself if choosing to have a sexual relationship abroad, and seeking help if one does experience any sexual violence abroad.

### Phase 2 RCT

A sample of 1200 eligible students will be randomly assigned via computer-generated random numbers to complete the intervention (N = 600) or control (N = 600). Participants will be randomly selected from the interested students for inclusion and randomized to the intervention or control conditions in a stratified fashion to ensure equal cells by gender (male, female), age (21+ and under 21), host country (European vs. non-European), and institution type (small college vs. large university). If randomized to the intervention condition, participants will immediately receive the intervention after completing the predeparture survey. Participants can view their feedback again if they desire and will be resent a link to their feedback via email during their first and last month abroad.

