### Procedures

Representatives from the study abroad offices at the 50 institutions will email prospective students to inform them about the study. Interested students will fill out an online sign-up sheet to assess eligibility. We will then randomly invite students into the study to ensure we have adequate numbers of both male and female genders represented. Invited students can consent to participate in the study and fill out measures collected online. Participants’ confidential data will be tracked by PIN codes. Participants will read an electronic IRB consent form and indicate consent before enrolling in the study. We will recruit 1200 participants who will be randomly assigned to the intervention condition (N = 600) or a control condition (N = 600). Intervention participants will receive the 30 to 40 min intervention as described below. Control participants will receive a link to a general website offering study abroad advice and will be asked to spend at least 30 to 40 min reviewing their institution’s study abroad website content, including policies for drinking abroad. This control condition was selected as a form of “treatment as usual” as our conversations with study abroad personnel indicated this is the extent of typical information students receive about alcohol use abroad. Many students also attend predeparture informational orientation sessions where alcohol use and sexual risk may or may not be briefly discussed; we will control for receipt of orientation sessions that cover such topics in analyses.

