Participants will complete a survey approximately 2 weeks prior to departure, one survey during their first month abroad, one during their last month abroad, one during their first month back in the US, and a final follow up 3 months post-return to the US. The last survey completed abroad represents the final 30 days of the trip, which, for the majority of students in the study, will be the third month abroad. Length of program will be controlled for in analyses. Participants will receive a $20 Amazon gift card for each of these 15 to 20 min surveys that they complete. Email, text, and phone call reminders will assist with reducing attrition on surveys, which helped us retain 80% of participants in our pilot work and other RCTs [52, 76]. A diagram of participant flow through the intervention study is found in Fig. 1. Figure 2 contains a SPIRIT (Standard Protocol Items: Recommendations for Interventional Trials) flow diagram of the RCT schedule of enrollment, interventions, and assessments.

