## Analytic plan

### Main effects of the PNF intervention

We will analyze five outcomes (total drinks per week, number of heavy drinking days, alcohol-related consequences, risky sex behaviors, and experience of any sexual violence victimization) within a multilevel modeling framework, with the level 1 units being measurement occasions, the level 2 units being individuals, and the level 3 units being schools. Our models will include random effects for the individual students as well as schools to properly adjust for correlations among the repeated measures within an individual student and the students attending the same US school. By analyzing within a multilevel framework, we can investigate whether the intervention is differentially effective at different time points. The main analysis is to estimate the effect of the intervention compared to control at each follow-up time (the first and last month abroad and 1- and 3- months post-return). The N of 1200 was determined in a priori power analyses to be sufficient to detect small to moderate intervention effect sizes for all primary outcomes.

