##### Heavy drinking and alcohol-related consequences

Three prespecified drinking outcomes are total drinks per week, number of heavy drinking occasions, and number of alcohol-related consequences in the past 30 days. Drinking in the past 30 days will be assessed at all time points with the Daily Drinking Questionnaire (DDQ; [79]), which asks participants about their typical drinking on each day of a typical week in the past month. It will be used to generate the main drinking outcome of drinks per week but will also yield drinking variable we will look at descriptively (typical drinks consumed per occasion, drinking days per week). A single item will also assess frequency of heavy drinking (5+ drinks on one occasion for males; 4+ drinks on one occasion for females; known in some studies as “binge drinking”). Consequences from alcohol use in the past month will be assessed on all surveys with the 24-item Brief Young Adult Alcohol Consequences Questionnaire (B-YAACQ), a measure of negative consequences often used with the college population [80, 81]. The scale assesses alcohol-related consequences experienced in the past month (yes/no) with a sum score from 0 to 24.

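### The article names only programme length and orientation receipt as adjustment covariates; the main models should also state and use the four stratification factors and the predeparture outcome values

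*Protocol article*

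**What the plan says.** - **Allocation** (Protocol article, Phase 2 RCT): students are "randomly assigned via computer-generated random numbers to complete the intervention (N = 600) or control (N = 600". The assignment is made "in a stratified fashion to ensure equal cells by gender (male, female), age (21+ and under 21), host country (European vs. non-European". The fourth stratification factor is the type of institution, which separates small colleges from large universities.
- **Main model** (Main effects of the PNF intervention): a three-level model of occasions within students within schools. "Our models will include random effects for the individual students as well as schools". The main contrast is intervention against control at each follow-up. The section lists no fixed covariates and does not say whether predeparture is one of the level-1 occasions.
- **Named covariates** (Procedures): "we will control for receipt of orientation sessions that cover such topics in analyses", and "Length of program will be controlled for in analyses".
- **Predeparture values** (Outcome measures): "Drinking in the past 30 days will be assessed at all time points with the Daily Drinking Questionnaire". The same holds for consequences: "Consequences from alcohol use in the past month will be assessed on all surveys with the 24-item". For risky sex a predeparture measure is implied by the equal past-month windows across surveys. Sexual violence at predeparture is lifetime history. Its follow-up measures cover the whole trip (last-month-abroad survey) and the period since return (3-month survey), so it has two follow-ups.
- **Moderators** (Mediator and moderator effects; Measures of moderators): all four stratifiers, baseline drinks per week and sexual violence history appear here, as interactions added to the main model.
- **Prognosis** (Other risk factors): being under 21, the destination and gender are each linked to drinking abroad.

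**The concern.** The factors that the article links to drinking, and on which it stratifies, are not among the covariates it names for the main effect. Stratifying on a prognostic factor makes the treatment estimate more stable. If the factor is then left out of the model, the reported standard error does not show that gain and the test runs below its nominal level. Leaving out a predeparture value of the same outcome gives up further precision that costs nothing to obtain.

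Two narrower issues go with this.

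- **Orientation receipt.** The predeparture survey falls about 2 weeks before departure and the intervention follows at once. An orientation session can therefore take place after allocation. The article does not say when receipt is recorded. Controls are sent to their institution's study abroad website and intervention students see alcohol and sexual-safety content, so attendance, or recall of what a session covered, could differ by arm. Conditioning on such a variable could bias the effect.
- **Baseline drinks per week.** If predeparture is an outcome occasion, the drinks-per-week moderation model has the same value as outcome and as predictor.

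**Working it through.** **The plan's own figure.** N = 1200 cannot be reproduced, because the article gives no alpha, power, effect size or SD. As a plausibility check, assume two-sided alpha 0.05, 80% power and SD 1:

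detectable difference = (1.960 + 0.842) × √(2/n per arm)

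- 600 per arm: 2.802 × √(2/600) = 0.162 SD.
- 480 per arm (the 80% retention cited from earlier work: 0.8 × 600): 2.802 × √(2/480) = 0.181 SD.

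The stated sensitivity to small-to-moderate effects is therefore plausible for continuous outcomes even without adjustment. School clustering is ignored here, since students are randomised individually.

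**Predeparture value as covariate.** The variance factor is 1 − r², where r is the baseline-to-follow-up correlation (assumed), with 480 analysed per arm:

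| r | 1 − r² | SE reduction | Detectable difference (SD) | Equivalent n per arm (480/(1 − r²)) | Power at a true 0.18 SD |
|---|---|---|---|---|---|
| no adjustment | 1.00 | – | 0.181 | 480 | 79.6% |
| 0.3 | 0.91 | 4.6% | 0.173 | 527 | 83.2% |
| 0.5 | 0.75 | 13.4% | 0.157 | 640 | 89.6% |
| 0.7 | 0.51 | 28.6% | 0.129 | 941 | 97.4% |

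**Predeparture as a level-1 occasion.** Generalised least squares with five occasions and compound symmetry, complete data, arm contrast at one follow-up:

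- Mean at predeparture common to both arms, arm effects at the four follow-ups: variance factors 0.91, 0.75 and 0.51 at r = 0.3, 0.5 and 0.7. These equal covariate adjustment.
- Arm effect left free at all five occasions: factor 1.00 at every r, so the gain is lost.

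**Stratifiers alone.** The variance factor is 1 − R², with R² assumed at 0.02 to 0.15:

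- SE reduction 1 − √(1 − R²): 1.0% at 0.02, 7.8% at 0.15.
- Detectable difference: 0.179 down to 0.167 SD.
- True level of a nominal 5% test that ignores the strata, 2 × [1 − Φ(1.960/√(1 − R²))]: about 4.8% at 0.02 and 3.4% at 0.15.

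The two gains do not simply add, because baseline drinking and the stratifiers are likely to share explained variance.

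**The case against.** The strongest reply is that silence is not a decision. A reader might infer that the plan rules these covariates out; no section does. The two covariate statements sit in Procedures, each answers one design issue, and neither claims to be the whole list. A complete list is commonly left to a fuller plan. That reply stands against any claim of an error, and N = 1200 is not shown to be wrong. It does not remove the point, because the article does describe its main model and does choose two covariates, while giving the prognostic and stratified factors a role only as moderators.

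Other replies also carry weight:

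- Predeparture may already be a level-1 occasion: drinking is measured at every time point and the effect is defined at follow-ups, which fits a common baseline mean. On that reading no baseline precision is lost.
- A reader might assume that every outcome has a like-for-like predeparture value. Sexual violence has only pre-trip history, and for risky sex the measure is implied.
- The article reports associations with drinking without their strength, and for age, destination and gender says nothing on the sexual outcomes. The school random effect may absorb part of institution type.
- 1 − r² is a linear-model result. For counts and the binary outcome it is only indicative.
- A reader might infer that orientation receipt is recorded after allocation and biases the result. The article leaves the timing open, so this is a risk to close off, not a demonstrated bias.

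**Conclusion.** The point holds as an inexpensive improvement to the stated analysis, with one risk to remove. With only the named covariates, omitting the stratifiers and baseline values would not bias the main effect; it would make it less precise and, because of the stratification, slightly conservative.

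The larger part of the possible loss is the predeparture value, and it arises only if that value is left out or if the arms are left free to differ at predeparture. The stratifiers alone matter less. Neither size can be derived from the article: both rest on assumed r and R² and on a linear outcome. The equivalence of 640 to 480 per arm at r = 0.5 (640/480 = 1.33) illustrates an assumption and is not a property of this trial.

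The orientation covariate is the one place where a named choice could do harm rather than forgo a gain, and only if receipt is recorded after allocation.

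**What to change.** 1. Include gender, age group, host region and institution type as fixed covariates in each main model.
2. State how the predeparture value enters. Either use it as a covariate, with that outcome's own follow-ups as the level-1 occasions (for sexual violence two follow-ups, with pre-trip history as the covariate), or, for outcomes measured the same way before departure, keep it as an occasion with a mean common to both arms.
3. In the drinks-per-week moderation model, do not let baseline drinks per week be both an outcome occasion and the moderator.
4. Adjust for orientation receipt only with a value recorded before allocation, or move that adjustment to a sensitivity analysis. Programme length can stay as named.
5. For binary and count outcomes, state the estimand, because the adjusted effect is conditional on the covariates.

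The cost is analysis-plan wording. The stratifiers and predeparture measures are already part of the design; at most one orientation item is added to the predeparture survey.

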#### PNF component

During the initial part of the intervention, participants will be asked to indicate how many drinks on average they think they will drink on a typical drinking day while abroad, as well as how many days in a typical month while abroad they will drink 5 or more for males/4 or more for females on an occasion (heavy drinking days). On-screen PNF will be presented containing information on the drinking behavior and attitudes about their gender- and country-specific study abroad peers in graphical and text format. As is standard in PNF interventions [78], a graph will display the participant’s intended drinking, their perception of the drinking of their gender- and country-specific peers, and the actual norm we have collected in Phase 1 (see example in Fig. 3). Text will also display moderate drinking norms (e.g., males students in China report drinking about 3 drinks per occasion”). This PNF format has been used in our prior work and with other event-specific prevention interventions targeting intended drinking behavior prior to high-risk events such as 21st birthday and spring break trips [41, 49, 50]. Participants will then watch video clips of students discussing that drinking among both peers and local people was moderate and less than they had expected before they went abroad.

**Fig. 3 Fig3:**
[figure not shown]
Example graph of PNF for a male student studying abroad in China

#### SAF component

The SAF-focused content of the intervention will be similar to what we used in our pilot work [52], which was developed through a thorough review of the literature on sojourner adjustment [55, 60, 77] and focus groups with students to generate tips and strategies for meeting goals of sojourner adjustment abroad. As noted above, we will enhance the SAF by making it more interactive through the use of video testimonials [77]. Participants will view text-based tips and strategies and watch clips of students discussing how they engaged with the culture while abroad. All content focuses around the four aspects of positive sojourner adjustment (social interaction with host nationals, cultural understanding and participation, language development and use, host culture identification) and the two negative sojourner adjustment factors while abroad (i.e., social interaction with co-nationals [(i.e., other Americans], homesickness/feeling out of place) [77]. These video testimonials were collected from eight students that had recently returned from study abroad experiences in several different countries. Students were selected based on diversity of race/ethnicity, gender, and location of study abroad. They were interviewed on campus using a structured interview based on the facets of sojourner adjustment [77]. Clips from these interviews were vetted with study abroad experts and selected based on sufficient coverage of the cultural engagement issues students may encounter while abroad.

#### Staying safe component

Based on review evidence-based approaches for sexual violence prevention back on campus [74, 75], we will include components to address safety behaviors while abroad in three areas: avoiding unwanted sexual experiences abroad, having a safe sexual relationship abroad, and seeking help if one experiences sexual violence or a negative sexual consequence abroad (e.g., contracting a sexually transmitted disease). The intervention will contain text-based tips and protective strategies to be used abroad to reduce sexual risk and sexual violence victimization, as well as clips of students discussing these tips and strategies and encouraging help seeking if one should experience sexual violence abroad. Strategies include having a plan to get out of a potentially unsafe situation, using protection if choosing to engage in sexual activity, ensuring that consent is received during sexual experiences, and looking out for friends and stepping in if they appear to be in a dangerous situation (bystander intervention). Video clips of students discussing methods they used to stay safe abroad will be included. All included content was vetted with research and clinical experts in sexual violence.

## Analytic plan

### Main effects of the PNF intervention

We will analyze five outcomes (total drinks per week, number of heavy drinking days, alcohol-related consequences, risky sex behaviors, and experience of any sexual violence victimization) within a multilevel modeling framework, with the level 1 units being measurement occasions, the level 2 units being individuals, and the level 3 units being schools. Our models will include random effects for the individual students as well as schools to properly adjust for correlations among the repeated measures within an individual student and the students attending the same US school. By analyzing within a multilevel framework, we can investigate whether the intervention is differentially effective at different time points. The main analysis is to estimate the effect of the intervention compared to control at each follow-up time (the first and last month abroad and 1- and 3- months post-return). The N of 1200 was determined in a priori power analyses to be sufficient to detect small to moderate intervention effect sizes for all primary outcomes.

#### Outcome measures

Primary outcomes of the intervention are prevention of heavy and problematic drinking abroad, prevention of risky sexual behaviors abroad, and prevention of any sexual violence victimization abroad. Any observed intervention effects seen during abroad on the first and last month abroad surveys are anticipated to sustain through the first- and third-month post-return to the US, such that intervention participants will drink less, experience fewer problems, engage in fewer risky sexual behaviors, and experience fewer sexual violence events than control participants in the 3 months following return from abroad.

##### Heavy drinking and alcohol-related consequences

Three prespecified drinking outcomes are total drinks per week, number of heavy drinking occasions, and number of alcohol-related consequences in the past 30 days. Drinking in the past 30 days will be assessed at all time points with the Daily Drinking Questionnaire (DDQ; [79]), which asks participants about their typical drinking on each day of a typical week in the past month. It will be used to generate the main drinking outcome of drinks per week but will also yield drinking variable we will look at descriptively (typical drinks consumed per occasion, drinking days per week). A single item will also assess frequency of heavy drinking (5+ drinks on one occasion for males; 4+ drinks on one occasion for females; known in some studies as “binge drinking”). Consequences from alcohol use in the past month will be assessed on all surveys with the 24-item Brief Young Adult Alcohol Consequences Questionnaire (B-YAACQ), a measure of negative consequences often used with the college population [80, 81]. The scale assesses alcohol-related consequences experienced in the past month (yes/no) with a sum score from 0 to 24.

